## Abstract

**Background:**

Cigarette smoking is the leading preventable cause of disease and death in the United States. Despite the availability of a plethora of evidence-based smoking cessation resources, less than one-third of individuals who smoke seek cessation services, and individuals using these services are often those who are actively contemplating quitting smoking. There is a distinct dearth of low-cost, scalable interventions to support smokers not ready to quit (ambivalent smokers). Such interventions can assist in gradually promoting smoking behavior changes in this target population until motivation to quit arises, at which time they can be navigated to existing evidence-based smoking cessation interventions. Conversational agents or chatbots could provide cessation education and support to ambivalent smokers to build motivation and navigate them to evidence-based resources when ready to quit.

**Objective:**

The goal of our study is to test the proof-of-concept of the development and preliminary feasibility and acceptability of a smoking cessation support chatbot.

**Methods:**

We will accomplish our study aims in 2 phases. In phase 1, we will survey 300 ambivalent smokers to determine their preferences and priorities for a smoking cessation support chatbot. A “forced-choice experiment” will be administered to understand participants’ preferred characteristics (attributes) of the proposed chatbot prototype. The data gathered will be used to program the prototype. In phase 2, we will invite 25 individuals who smoke to use the developed prototype. For this phase, participants will receive an overview of the chatbot and be encouraged to use the chatbot and engage and interact with the programmed attributes and components for a 2-week period.

**Results:**

At the end of phase 1, we anticipate identifying key attributes that ambivalent smokers prefer in a smoking cessation support chatbot. At the end of phase 2, chatbot acceptability and feasibility will be assessed. The study was funded in June 2022, and data collection for both phases of the study is currently ongoing. We expect study results to be published by December 2023.

**Conclusions:**

Study results will yield a smoking behavior change chatbot prototype developed for ambivalent smokers that will be ready for efficacy testing in a larger study.

**International Registered Report Identifier (IRRID):**

DERR1-10.2196/44041

## Introduction

Cigarette smoking continues to be the leading preventable cause of disease and death globally and in the United States [1]. Cigarette smoking kills more than 480,000 Americans each year and results in more than US $240 billion in health care spending and nearly US $372 billion in lost productivity [2]. Thus, promoting smoking behavior change with the long-term goal of achieving successful cessation is critical to reducing the public health impact caused by tobacco use. Within the United States, the past few decades have seen a groundswell of evidence-based interventions to quit smoking. These have included a wide range of strategies such as mobile health (mHealth) apps [3,4], availability and increased access to effective pharmacotherapy for cessation [5], SMS text messaging support [6,7], evidence-based behavioral counseling [8], and comprehensive state-based programs, such as tobacco quitlines [9,10]. However, despite their widespread availability, less than one-third of people who smoke cigarettes actively avail themselves to cessation strategies [11]. For example, tobacco quitlines—free evidence-based smoking cessation programs providing telephone-based behavioral counseling combined with cessation pharmacotherapy available in all 50 US states—are used by less than 3% of people who smoke [12]. One potential reason for the low uptake of existing services for cessation may be that strategies to promote cessation differ according to an individual’s readiness and motivation to quit [13]. Although smokers actively committed to quitting respond positively and engage with cessation services, ambivalent smokers (ie, those not actively seeking treatment) may benefit from approaches that promote modest changes or “behavioral *nudges*” toward smoking behavior change (but not cessation) [14,15]. Most cessation research is focused on those expressing an intention to quit, and research on promoting behavior change in ambivalent smokers (not actively thinking about quitting) is scant.

A conversational agent or “chatbot” is an inexpensive and scalable approach to deliver personalized health information in a human-like manner. Common in the consumer-service sector, chatbots are increasingly being deployed in the health sector to provide education, support, service navigation, and interventions for a range of health issues, from COVID-19 to asthma [16,17]. Human-delivered interventions for smoking behavior change are effective but are resource-intensive, lack scalability, and can be expensive to implement. Chatbots have the intuitive appeal of being low-cost automated interventions that can widely reach ambivalent smokers. Moreover, chatbots can provide “virtual accompaniment” at the frequency and duration preferred by the smoker until the motivation to quit arises, at which time they can be swiftly connected to an existing evidence-based cessation intervention. A few studies on chatbots for smoking behavior change target participants actively intending to quit smoking [18-20] and, while important, only address the tip of the iceberg in terms of reaching the smoking population. Since motivation to quit smoking is dynamic and occurs along a continuum [21], strategies to engage ambivalent smokers may be most helpful if they are tailored to accommodate smokers’ changing preferences and are responsive to rapid changes in motivation (eg, connecting smokers to quitlines when ready to quit), while focusing on evidence-based strategies that have been effective for smoking reduction leading to cessation (eg, quit tips, self-monitoring, and tracking savings). Since interventions to assist smokers ambivalent about quitting are in their infancy, little is known about key elements of a chatbot-based smoking behavior change intervention tailored for this target population.

To overcome these gaps in the field, the goal of our study is to test a proof-of-concept of a novel chatbot to support and engage smokers who are not actively engaged in a quit attempt (ambivalent smokers). We propose accomplishing our aims in 2 phases. In phase 1, we will identify the key attributes that will guide the development of the chatbot prototype. We will survey ambivalent smokers to determine their preferences and priorities for a smoking cessation support chatbot. Using conjoint analysis, we will systematically elicit participant preferences for the proposed chatbot prototype (see details below). Grounded in macroeconomic principles [22], conjoint analysis is a quasi-experimental approach that decomposes a product or service into its key attributes, then poses the attributes to patients to understand patient-determined values for each attribute [23,24]. These preferences will be programmed into the chatbot prototype. In phase 2, we will invite participants to use the prototype over a 2-week period to assess the feasibility and acceptability of the developed chatbot prototype.

## Methods

### Study Overview

To develop the chatbot prototype (phase 1), we will recruit 300 participants who identify as current cigarette smokers to complete a web-based survey. The survey will collect demographics, smoking behavior history, and e-cigarette use, and solicit preferences for the most important features of the proposed chatbot. The top 5 preferred attributes will be used to design and develop the chatbot prototype. In phase 2, 25 participants will be recruited to engage with the developed prototype for a 2-week period. Preliminary acceptability and feasibility data will be collected via validated questionnaires at the end of 2 weeks. For both study phases, participants will be recruited using an established survey panel (Prolific). Study eligibility criteria are as follows: older than 18 years, self-report any smoking in the last 7 days, and no current intention to quit smoking in the next 30 days (score of ≥5 on a 10-point Likert scale assessing likelihood to quit smoking).

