### Phase 1: Development of Chatbot Prototype

#### Overview

This phase is designed as a cross-sectional survey to develop a prototype of the proposed chatbot by assessing preferred attributes in a sample of individuals ambivalent about quitting smoking. To do so, 300 participants have been identified who will be invited to complete a web-based survey. Participants will be recruited using the internet and an established study panel (Prolific). After completing a web-based informed consent, participants will provide information on demographics and smoking history, after which they will be provided with a brief explanation of chatbots (what they are and how they work). They will also be asked about their previous and current experience with chatbots and interest in a chatbot designed to support people who may decide to quit smoking in the future.

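### As printed, the numeric cut-off for having no intention to quit runs opposite to the verbal criterion it defines, unless the item is reverse-scored, which the protocol does not say

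*Protocol article*

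**What the plan says.** The intention criterion appears once, in Methods, Study Overview, and applies to both phases. Eligible smokers must have "no current intention to quit smoking in the next 30 days (score of ≥5 on a 10-point Likert scale assessing likelihood to quit smoking"). The parenthesis defines the words before it. The scale's anchors and scoring direction are not given there or anywhere else in the article.

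The target population is described several times, each time as smokers with low or no present intention to quit:

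- The Abstract (Background) speaks of a lack of interventions to "support smokers not ready to quit (ambivalent smokers").
- The Introduction says that "research on promoting behavior change in ambivalent smokers (not actively thinking about quitting) is scant", and gives the study goal as supporting and engaging "smokers who are not actively engaged in a quit attempt (ambivalent smokers").
- The Phase 1 Overview describes the survey as "assessing preferred attributes in a sample of individuals ambivalent about quitting smoking".
- The Discussion says that the model is meant for people who are not actively considering quitting.

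**The concern.** The parenthesis is meant to turn the verbal criterion into a screening rule. On its plain reading it does the reverse: on a scale that measures how likely someone is to quit, a floor of 5 lets in the likeliest quitters and shuts out the least likely.

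The rule decides whose preferences the study measures. Phase 1 preferences determine which features go into the prototype, and phase 2 participants are drawn from phase 1 respondents who express interest, so a selection error in phase 1 would carry into the acceptability and feasibility ratings. The article also distinguishes itself from a few earlier chatbot studies, which enrolled people actively intending to quit. A screener that followed the plain reading would admit such people and exclude the smokers furthest from quitting.

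**Working it through.** No sample-size, power or error-rate figure is involved. The check is to list which scores the rule admits under each possible scoring direction and compare them with the words.

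**Inputs**

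- Verbal criterion: no intention to quit in the next 30 days (Study Overview).
- Numeric rule: score of 5 or more, 10-point scale, construct is likelihood to quit (Study Overview).
- Scoring direction: not stated.
- Score range: not stated; 1 to 10 assumed, so the midpoint is (1 + 10)/2 = 5.5.

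**Direction A: higher score means more likely to quit (the plain reading)**

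- Admitted: 5, 6, 7, 8, 9, 10, which is 10 − 5 + 1 = 6 of 10 points. This includes every score above the midpoint and the maximum.
- Excluded: 1, 2, 3, 4, which is 4 of 10 points and the lowest likelihoods of quitting.
- Compared with the words: opposite.

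**Direction B: higher score means less likely to quit (reverse-scored, not stated)**

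- Admitted: 5 to 10, now the less likely end, apart from 5 itself, which lies 0.5 below the midpoint.
- Excluded: 1 to 4, now the likeliest quitters.
- Compared with the words: the direction agrees.

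**Sensitivity to the assumed range.** If the ten points run from 0 to 9, the rule admits 5 to 9 (9 − 5 + 1 = 5 of 10 points) and excludes 0 to 4. Under direction A it still keeps the top of the scale and drops the bottom, so the contradiction does not depend on the range.

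**Consequence if direction A was used in the screener.** Everyone enrolled has a score of 5 or more. The corrected rule under direction A would require a score below 5. The two sets do not overlap, so no enrolled respondent would meet the corrected criterion, and re-analysing an eligible subset would not be possible.

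**Reach.** The rule applies to the 300 phase 1 participants and the 25 phase 2 participants.

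**The case against.** The strongest reply is that a journal article often leaves item wording and anchors to the full protocol. The item may be reverse-scored, or the inequality sign may simply be misprinted while the live screener is right. That reply stands as far as enrolment goes: a reader might infer that the sample consists of smokers intending to quit, and the article does not support that. It does not remove the point about the text. The article does more than omit a detail. It prints a threshold and names a construct that together contradict the criterion, and nothing in it says that the item is reversed.

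Two further inferences are tempting and should not be drawn.

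- One is that the rule fails even on a reverse-scored scale because 5 lies just below the midpoint. Under reverse scoring the direction is right. Only that single score falls on the likely side, and objecting to it is a preference about where to cut, not an error. The documents give no basis for a stricter threshold.
- The other is that the plain reading excludes the whole target population. The article's descriptions of ambivalence are broad, and people scoring 5 or 6 remain eligible and could fairly be called ambivalent. What the plain reading excludes is the group least likely to quit.

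**Conclusion.** The point holds as an internal contradiction that must be corrected. Read plainly, the only stated operational rule for intention admits the highest likelihoods of quitting and excludes the lowest, contrary to its own verbal definition and to the target population in the Abstract, Introduction and Discussion. On an assumed 1 to 10 range this is 6 points admitted and 4 excluded, at the wrong ends. The conclusion rests on taking a scale of likelihood to quit to rise with likelihood. It would fall away under reverse scoring, which the article does not state. Confidence is high that the text as printed is wrong or incomplete. Whether the wrong people were enrolled cannot be judged from the article.

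**What to change.** 1. State the scale anchors and the scoring direction in the eligibility criterion.
2. Make the cut-off agree with the words. If higher means more likely to quit, reverse the inequality so that scores below 5 are eligible. If the item is reverse-scored, keep the present cut-off and say so.
3. Check the live panel screener now, since the Results section says that data collection is ongoing and the rule governs both phases.
4. If the screener did admit scores of 5 or more with higher meaning more likely, correct it for the remaining recruitment. Describe the preferences and acceptability ratings already collected as those of smokers with a moderate to high likelihood of quitting, not of smokers with no intention to quit.

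The cost is one line of text and one check or change of the screener filter. If the wrong direction was used, there is also a narrower population claim for the data already collected.

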### Ethics Approval

All study procedures have been approved by the University of South Florida’s Institutional Review Board (IRB # 004183). For phase 1, the data are deidentified with participants only providing a prolific ID. For phase 2, participant names and phone numbers will be stored on a password-protected computer only accessible to the study staff. All participants will be identified by a study ID and any identifying information will be removed from interview transcripts prior to beginning qualitative data analysis. Participants will be compensated for both phases of the study. Participants will receive US $6 for completing phase 1 and US $70 for completing phase 2.

### Phase 1: Development of Chatbot Prototype

#### Overview

This phase is designed as a cross-sectional survey to develop a prototype of the proposed chatbot by assessing preferred attributes in a sample of individuals ambivalent about quitting smoking. To do so, 300 participants have been identified who will be invited to complete a web-based survey. Participants will be recruited using the internet and an established study panel (Prolific). After completing a web-based informed consent, participants will provide information on demographics and smoking history, after which they will be provided with a brief explanation of chatbots (what they are and how they work). They will also be asked about their previous and current experience with chatbots and interest in a chatbot designed to support people who may decide to quit smoking in the future.

Next, we will administer a choice-based conjoint (CBC) analysis experiment to understand participants’ preferences for a smoking cessation chatbot. Using Sawtooth Software’s web-based choice analytics survey platform, we will construct hypothetical smoking cessation chatbot “scenarios” comprising the following six attributes (ie, potential chatbot features) with varying levels: (1) number of cigarettes smoked per day tracked (yes or no), (2) smoking quit-tips provided (yes or no), (3) money saved by reducing smoking tracked (yes or no), (4) mood tracking (yes or no), (5) smoking cravings tracked (yes or no), and (6) mental health screening and resource provision (only depression screening, only anxiety screening, or no mental health screening). These attributes were chosen a priori based on published smoking cessation literature identifying evidence-based strategies to promote and support smoking behavior change. The sixth attribute, mental health screening, was added given the comorbidity between smoking and mental health [25,26]. In the CBC experiment, participants will be presented with a series of tasks; each task will display 3 different chatbot configurations composed of identical attributes but differing combinations of attribute levels. A total of 10 tasks will be presented to participants. Each question will contain 3 panels that present a combination of the attributes and associated scenarios, and participants will be asked to choose the chatbot configuration they would most prefer (ie, the chatbot that contains the combination of chatbot attribute levels most desired). Participants may also choose “none” if no chatbot configuration presented is desirable. Figure 1 displays examples of the CBC tasks. Finally, the desired frequency of chatbot messages will be assessed, and at the end of the survey, interest in participating in phase 2 will be elicited.

**Figure 1 figure1:**
[figure not shown]
Examples of a conjoint analysis task.

#### Measures

For phase 1, assessments will include demographics (eg, age, sex, gender identity, and education) and smoking history (age of smoking initiation and number of previous quit attempts in the past year) [27]. Nicotine dependence will be measured by the Fagerstrom Test of Nicotine Dependence [28], which is a validated and ubiquitous instrument assessing dependence on nicotine. Smoking cessation self-efficacy will be measured using the validated Smoking Abstinence Self-Efficacy Questionnaire [29]. This 12-item questionnaire measures an individual’s self-reported confidence in resisting the urge to smoke in various settings and conditions. Given the high prevalence of e-cigarette use among individuals who smoke [30], current e-cigarette use will also be assessed [31]. In addition to these measures, we will also collect information on current use and frequency of marijuana or cannabis [32] and alcohol use [33].

#### Data Analysis

Summary statistics (mean [SD] or frequency [%]) will be calculated for demographic and smoking characteristics. For the CBC data analysis, also completed using Sawtooth Software [34], utility scores will first be computed to determine the relative desirability of each level within each attribute. These data will inform which of the chatbot feature levels were most desired (eg, whether a cigarette tracking feature is desired). Next, the relative attribute importance scores (ie, the relative impact of each attribute in respondent choices) will be computed; these data will indicate the order of importance of each of the 6 chatbot features (most important to least important). We will also compute the 95% CIs for each of the attribute scores. Finally, CBC data will be examined for variance by select sociodemographic variables (eg, sex, gender, education, and number of quit attempts) to determine possible chatbot preference differences by population segments. The combined data will inform the prioritization of chatbot features programmed into the prototype chatbot tested in phase 2.

### Phase 2: Acceptability and Feasibility Testing of the Chatbot Prototype

#### Overview

For phase 2, 25 eligible individuals expressing interest to participate at the end of phase 1 will be recruited to engage with the developed chatbot prototype. Participants will be contacted by the study staff to explain study procedures and complete informed consent, following which the participant will receive a link to complete a baseline survey. Following completion of the survey, they will be scheduled for an appointment to participate in a 45- to 60-minute interview conducted via secure videoconferencing. During this time, study staff will share a link with the participants to activate the chatbot prototype. An overview of the chatbot will be provided, following which participants will verbalize their thoughts and reactions while interacting with the chatbot, based on the think-aloud usability testing technique [32], and provide initial feedback while interacting with the chatbot. The interview will be audio and video recorded and participant interactions with the chatbot will be observed. At the end of this session, participants will be encouraged to use the chatbot over a 2-week period, engaging and interacting with the programmed attributes and components. To increase retention during this period, data entry and chatbot engagement will be monitored on a frequent basis, and all participants will receive daily reminders to engage with the chatbot. At the end of the 2-week period, participants will complete acceptability and feasibility assessments, provide feedback to open-ended questions to identify any aspect of the chatbot that was confusing, what they liked or disliked, perceived helpfulness of the chatbot, feedback on features they would like included, and aspects that would help keep them engaged with the chatbot. Participants will receive a total of US $70 for phase 2 (US $20 for the interview and US $50 after completion of the follow-up surveys).

#### Measures

In addition to the measures used in phase 1, phase 2 measures will include intervention acceptability using the Acceptability of Intervention Measure, Intervention Appropriateness Measure, and Feasibility of Intervention Measure [33], as well as intervention usability using Health Information Technology Usability Evaluation Scale [35].

